#### WP6: health economic evaluation

For the quantitative validity testing of the outcomes measures, we will calculate completion rates of the measures and items. For the qualitative validity testing, we will code the think-aloud interview transcripts to identify errors or difficulties in responding to items. Mean pre and post quality of life scores will be used to estimate quality of life benefits from the interventions. These data will be combined with estimates of the intervention costs in a simple cost–consequence analysis.^62^

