### Year 2: feasibility testing

Lay counsellors will be from the local areas, have at least a master’s qualification in psychology or a related discipline and experience in working with young people and/or schools. Prior to the launch of the feasibility study, they will receive full training over 3 months by a clinical psychologist on the team, supported by another team member experienced in training lay counsellors. Trainees will deliver multiple mock sessions of intervention delivery to support readiness for delivery in schools and quality control. The feasibility study will run in eight schools, with three randomly assigned to waitlist. The four interventions will run in parallel in schools. Lay counsellors will complete weekly monitoring logs of intervention delivery in each school, including logging of modifications made (as per FRAME^48^) and will have weekly supervision by clinical team members. Fidelity monitoring will be undertaken by a team of trained data collection assistants who have been heavily involved in the intervention development stage and will be highly familiar with the implementation protocol. Fidelity monitoring reports will be discussed frequently with the research manager to identify needs for lay counsellor action/support or intervention modification (see WP5).

We have established preliminary feasibility indicators for each intervention, which will be updated when interventions are finalised. Feasibility indicators which will be common across WP1–4 interventions are: meeting recruitment and retention rates, delivery as intended, measure completion and no significant adverse effects. We will adopt a ‘traffic light’ system for recruitment and retention as follows: red—if rates below 50% (say) then will not proceed; amber—if rates 50%–65% then proceed if there are plans to improve; green—above 65% proceed to definitive trial. Mixed-methods process and evaluation data will be secured for all interventions from adolescents, teachers, parents and lay counsellors to explore: perceived usefulness of the interventions; implementation challenges; unintended negative effects; safeguarding challenges; the process of change and intervention development needs. Evaluation outcomes will inform intervention improvements and parameters for a definitive trial.

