#### WP6: health economic evaluation

Using a micro (bottom-up) costing strategy,^54^ separate design and delivery costs per intervention component will be estimated using available data sources (eg, government ministry data, national pay scales, national earnings surveys) to determine unit costs for personnel time. Any additional primary data needs will be identified. Costs will be presented at the class and school level to promote generalisability. Preference-based outcome health and well-being measures are needed for economic evaluation^55^ but there is limited evidence on their use with adolescents and no evidence of their use feasibility in this context (with adolescents in school-based settings and in India). We will feasibility test candidate measures including Child Health Utility (CHU)-9D^56^ and EQ-5D-Y^57^ via pre–post administration to 50 intervention adolescents and via 10 think-aloud interviews to identify completion challenges (a satisfactory sample size given the richness of interview data). We will also administer the EQ-5D-5L^58^ and the ICEpop CAPability measure for Adults (ICECAP-A)^59^ pre and post intervention to 50 parents to determine measure completion and any need for instrument adaptation. These sample sizes are not selected to estimate the significance of a specific outcome, but to balance the desire to not overburden individuals while still informing completion rates of instruments and items. We will use the cost and outcome data to generate exploratory cost–consequence analyses of the intervention strategies.

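### WP6 labels uncontrolled pre-post change in 50 intervention pupils as quality-of-life benefit, although a randomised waitlist arm could supply the comparison

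*Protocol article*

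**What the plan says.** The article has two WP6 sections. The methods section tests CHU-9D and EQ-5D-Y "via pre–post administration to 50 intervention adolescents", with 10 think-aloud interviews alongside. It also gives EQ-5D-5L and ICECAP-A "pre and post intervention to 50 parents to determine measure completion and any need for instrument adaptation"; the parents' arm is not stated. It explains that "These sample sizes are not selected to estimate the significance of a specific outcome", the aim being to limit burden while learning about completion. It adds: "We will use the cost and outcome data to generate exploratory cost–consequence analyses of the intervention strategies".

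The WP6 section of the Data analysis plan gives the estimator and its interpretation: "Mean pre and post quality of life scores will be used to estimate quality of life benefits from the interventions". It continues: "These data will be combined with estimates of the intervention costs in a simple cost–consequence analysis". Neither section names a waitlist comparison.

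A comparator does exist. Under Year 2: feasibility testing, "The feasibility study will run in eight schools, with three randomly assigned to waitlist". The Sample size calculation section expects 288 waitlist pupils alongside 480 intervention pupils at 80% recruitment and compares mean SDQ change between the groups. The WP1–5 feasibility analysis regresses 3-month outcomes on baseline.

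**The concern.** A mean change in a single arm cannot be divided into the part the intervention caused and the part that would have happened anyway. Over a school term the second part can include the point reached in the academic year (the Introduction itself stresses academic pressure), familiarity with the questionnaire, and other events common to all schools. It can run in either direction, so it could create an apparent benefit or hide a real one.

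What is at stake is the outcome side of the cost-consequence table. Such a table is read as cost against effect, and the Year 2 section says evaluation outcomes will inform the parameters of a definitive trial. A figure labelled as benefit that contains an unknown amount of background change could mislead that step. The completion-rate and think-aloud aims do not depend on it.

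**Working it through.** **No WP6 figure to reproduce.** The 50 is expressly not the result of a power calculation, and the article gives no SD for any preference-based measure. Precision is therefore expressed in units of the SD of individual change.

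**Is there a usable waitlist group?** Inputs from Sample size calculation and Year 2: 960 pupils approached, five of eight schools intervention, three waitlist.
- 80% recruitment: 960 × 0.80 × 5/8 = 480 and 960 × 0.80 × 3/8 = 288, matching the article.
- 65% recruitment: 960 × 0.65 × 5/8 = 390 and 960 × 0.65 × 3/8 = 234.

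**What each estimator targets.** Let e be the intervention effect and d the change that would have occurred without it.
- Pre-post change in intervention pupils estimates e + d, so its bias is d.
- The between-arm difference in change estimates e, provided d is common to both arms.

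**Precision, ignoring clustering.**
- Pre-post, 50 pupils: SE = √(1/50) = 0.141; 95% half-width 1.96 × 0.141 = 0.28.
- Adding 30 waitlist pupils: SE = √(1/50 + 1/30) = 0.231; half-width 1.96 × 0.231 = 0.45.
- Splitting the same 50 about 31/19: SE = √(1/31 + 1/19) = 0.291.

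**Precision with clustering.** Assume 10 pupils per school (five schools against three) and an ICC for change of 0.01 to 0.05; the documents give neither figure. The design effect is 1 + 9 × ICC, that is 1.09 to 1.45.
- ICC 0.01: SE = 0.231 × √1.09 = 0.241.
- ICC 0.05: SE = 0.231 × √1.45 = 0.278.
- With 8 − 2 = 6 degrees of freedom (t = 2.447), the 95% half-widths are about 0.59 and 0.68.

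These use simple differences in change. Baseline adjustment should do no worse in large samples, because its residual SD is no larger than the SD of change.

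**Trade-off.** On mean squared error, the controlled estimate with 30 waitlist pupils is better once d² exceeds the added variance. Ignoring clustering, this is d > √(1/30) = 0.18 SD. With ICC 0.05 it is d > √(1.45/30) = 0.22 SD. Without waitlist data, nobody can tell on which side of that line d lies.

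**The case against.** The strongest reply is that WP6 claims little. The analysis is labelled exploratory, the sample was chosen for completion rates and burden, and the progression criteria rest on recruitment, retention, delivery, measure completion and adverse effects. None uses the WP6 change. All of this stands, and it limits the seriousness of the point. It also defends the sample size. It does not defend the causal label, because a sample not chosen to estimate an outcome is a weak basis for calling its change a benefit.

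A second reply is that quality of life is a WP1 secondary outcome, so an arm comparison may be made there. That is possible, but the article names no WP1 instrument for it, and WP6 does not refer to it. It would go too far to infer that quality of life is never compared between arms.

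Third, a controlled estimate from three waitlist schools would be imprecise and could not firmly separate the intervention from school differences. This is correct and is the main cost of the larger fix.

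A reader might infer that a modest background shift would be declared a significant benefit. The plan proposes no significance test on these scores, so the documents do not support that reading. Nor do they support regression to the mean as a main mechanism: the programme is universal, and nothing says the 50 are chosen on their scores.

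Finally, one might say the detail belongs in an unseen full protocol. The article itself, however, fixes the sample, the arm, the estimator and the interpretation.

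**Conclusion.** The point holds as a cheap and worthwhile improvement to an exploratory analysis. As written, WP6 attributes all change over time in 50 intervention pupils to the interventions, and nothing elsewhere in the article corrects this. The bias equals the background change; its size and direction are unknown and cannot be estimated from the planned WP6 data.

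It would be wrong to infer that WP6 is unsound as a whole or that 50 is too few: that number serves the completion aim. It would also be wrong to infer that the parents are all from intervention schools. For them, the point is only that no comparison is described.

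The precision figures rest on assumed waitlist numbers, 10 pupils per school and an assumed ICC of 0.01 to 0.05.

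**What to change.** **Minimum.** In the WP6 section of the Data analysis plan, report mean pre and post scores descriptively and remove the statement that they estimate benefit from the interventions. This costs nothing.

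**Preferred, in addition.** Give CHU-9D and EQ-5D-Y to a subsample of waitlist pupils, for example about 30 (10 in each of the three schools), at the baseline and 3-month assessments already planned. Keep all 50 intervention pupils, because splitting them across arms would weaken the completion aim and give a less precise contrast. Enter the baseline-adjusted between-arm difference with its confidence interval in the cost-consequence table, marked exploratory, and state that only three waitlist schools contribute.

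The cost is 30 × 2 × 2 = 120 short questionnaires, some added respondent burden (which WP6 rightly weighs) and a wide interval. It would also show how the measures perform in control pupils, which a definitive trial needs to know.

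**Parents.** State which arm the 50 come from. Do not interpret their pre-post change as intervention benefit unless a waitlist comparison is made.

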#### WP7: understanding barriers and opportunities for research to policy uptake

Data from the stakeholder analysis and document reviews will be continuously triangulated with analysis of transcripts from the in-depth interviews. All qualitative data will be analysed using framework approach^58^ and guided by the three questions for WP7 and relevant theoretical frameworks for evidence-informed policy-making.^63–66^

### Patient and public involvement

Throughout SAMA, listening to adolescents will be central and incorporated in each WP. There are many barriers to adolescent involvement in low resource settings.^31^ These can include high levels of mental health stigma as well as cultural differences where adolescents' opinions might be less commonly sought and heard. Our approach to adolescent participation will be informed by the WHO Global Consensus Statement on Meaningful Adolescent & Youth Engagement.^67^ Adolescents will be trained and supported to contribute to the project. As well as being involved as participants in the design and evaluation of interventions in WP1–5, other adolescents will sit our Youth Advisory Board to act as ‘critical friends’ of the project. Adolescent contribution will also be via participatory filmmaking. This is a key platform within and beyond our project for youth voice in India on adolescent mental health and the role of schools in well-being. Other stakeholders including parents, teachers, the school community and policy-makers will be involved in the codesign and evaluation stages of the study.

### Ethics and dissemination

This research is being conducted in community settings and has received ethical approval from the National Institute of Mental Health Neurosciences Research Ethics Committee (NIMHANS/26th IEC (Behv Sc Div/2020/2021)), and the University of Leeds School of Psychology Research Ethics Committee (PSYC-221). Additional approvals have been granted by the Karnataka state primary and secondary education ministry and the Karnataka Department of State Education Research and Training.

We will seek consent from parents, teachers, school staff and other stakeholders and assent from adolescents. Grade 9 pupils will receive WP1 and 3 but can opt out of data collection. This is to ensure that participants’ rights are not undermined by universal delivery. Teachers can access WP2 training without consenting to data collection. This is in recognition of the sensitivity of teachers reporting their mental health knowledge or use of harsh discipline practices, and responses will inform our understanding of the acceptability of our data collection measures. Audio/video recording in workshops and for WP8 will require explicit consent. Research data will be kept secure and confidential, with agreed UK–India data management plans and data sharing agreements.

Alongside WP1–5, we will be drafting, and refining through codesign, a stepped response and referral protocol to be assessed as part of the feasibility study. This protocol will draw on national and international guidance, as well as established practice in NIMHANS. Our priorities are response protocols for identification of (1) moderate-to-serious mental health need or risk (especially suicide risk) and (2) abuse (especially sexual abuse). The iterative production and field testing of this school mental health safeguarding policy will be an important contribution to the research field as well as to school systems.

Our plans for dissemination include: (1) events—launch, film screening, impact and capacity building events; (2) website—project website with multiple functionalities to engage, share resources, disseminate findings and in ways that can be sustained beyond the project; (3) social media (Twitter and Instagram) to reach multiple sectors and adolescents; (4) project briefs/updates/newsletters (flyers), especially for schools and community organisations; (5) executive reports to key stakeholders (eg, education and health departments, teacher training colleges, mental health service providers); (6) sharing the project on global repositories, such as the Mental Health Innovation Network; (7) using existing communication platforms from University of Leeds Global Challenges projects relevant to adolescent well-being in LMICs; and (8) conferences and peer-reviewed publications.

### Strengths and limitations

A key strength of the study is our systems approach.^12^ We target multiple risk and protective factors in the school setting as mental health is determined by both individual factors and the circumstances in which adolescents are living their day-to-day lives. A further positive about the study is its focus on anxiety and depression, which are the most common adolescent mental health conditions in India.^5 6^ The likely feasibility and efficacy of the SAMA interventions is strengthened by several aspects of study design. Youth voice is central with the use of Youth Advisory Board and filmmaking. We combine learning from SEHER^26 33^ with umbrella and systematic reviews of existing school interventions. Extensive investment is planned in intervention coadaptation/codesign with adolescents, schools, parents and key stakeholders, guided by established frameworks, to promote cultural relevance, ownership and acceptability.^37 38^ Our whole-school approach fosters school ownership, is inclusive, minimises stigma, and acceptability of lay counsellors as delivery agents is established.^33^ Inclusion of different school types and locations add to the potential generalisability of findings, and the use of validated and globally used instruments supports the generation of reliable and comparable data, including health economics data. Indian youth involvement, either as coresearchers, codesigners or in advisory panels, remains relatively novel. We will gain new insights into what works in this domain by supporting youth voice through advocacy via social media, filmmaking and pathways to policy impact. There are a number of study limitations. Study recruitment and engagement may be affected by school disruption from the COVID-19 pandemic, and the opt-in approach to consent may lead to participation bias. The universal approach with grade 9 students limits the extent to which interventions can be tailored to, for example, other mental health conditions or gender. We will be unable to identify adolescents with neurodevelopmental conditions or particular learning needs, meaning we will not know if they in particular can benefit from the interventions. Our school sampling strategy does not include representation of all possible Indian school structures and cultures.

## Discussion

In India, a key contextual determinant of adolescent mental health is the nature of schooling.^13–22^ This codesign and feasibility study is an important step towards an integrated, multicomponent whole-school approach to adolescent mental health in Indian secondary schools. School-delivered well-being programmes have the potential to exceed the reach and scalability of mental healthcare systems in LMICs.^8–10^ By targeting adolescent anxiety and depression, the interventions produced in SAMA will contribute to public mental health approaches to common adolescent mental health conditions in India, and, by promoting well-being factors, can inform health promotion strategies. Unique outcomes of the study include rich data on what Indian schools, and their communities, need and want from a whole-school approach to mental health as well insights into what aspects of international programmes need particular cultural adaptation. Mental health literacy among Indian adolescents, parents and teachers has been reported as low.^18–20^ Our study will generate new knowledge on whether programmes developed in other countries, with likely different conceptualisations of mental health and responses to it, can be successfully coadapted to be acceptable and helpful in Indian schools. By adopting a randomised controlled waitlist design, the study will generate a solid evidence base for progression to a randomised controlled trial and inform understanding of the acceptability and rigour of data collection instruments and process evaluations in complex intervention studies in Indian schools. To date, school initiatives in India have mostly targeted physical health and life skills.^24–27^ Drawing on the expertise of an international, interdisciplinary team, this study aims to contribute to the evidence base about what works in Indian schools to support adolescent mental health, and in particular, to reduce the prevalence and severity of adolescent anxiety and depression.
